#### 2.1.2. Secondary Endpoints

To evaluate the local recurrence rate, pain control, quality of life and electrochemotherapy toxicity.

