### 2.2. Subject Selection

Eligible patients will be randomly assigned (1:1) to the treatment group or the control group. The treatment group assignment will be assigned blindly and sequentially in the order in which eligible patients are enrolled in the study. Patients eligible for inclusion in the protocol (see Table 1) will be informed in detail about the study and, if they consent to participate, they will sign the informed consent form (Appendix A), witnessed by a member of the research group.

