### 2.5. Description of Study Procedures

Quality of life (QoL), as measured by the EQ5d questionnaire, will be completed at Visits 1, 2, 3, 5, 6, 7, 8, 9, 10, 11 and 12 and will be considered optional from visit 13 to 18. The EQ-5D was developed in Europe and it is a descriptive system of preference-based Health Related Quality Life [30]. The EQ-5D questionnaire also includes a VAS, by which respondents can report their perceived health status with a grade ranging from 0 (the worst possible health status) to 100 (the best possible health status). Pain will be assessed at Visits 1, 2, 3, 5, 6, 7, 8, 9, 10, 11 and 12.

#### 2.5.1. Visit 1

All patients will undergo the same enrollment/baseline visit (Visit 1) procedures. Clinical examination will include the measurement of weight, height and vital signs (pulse, blood pressure). Patients must sign the informed consent form. The Screening/Enrollment Visit (Visit 1) procedures must be performed not more than 12 (±1) weeks after the end of neoadjuvant therapy. Patients who fulfill all inclusion criteria will be enrolled. Patients who are Eastern Cooperative Oncology Group ECOG (ECOG) Performance Status grade 0, 1 or 2 are eligible for study participation [31].

Study procedures at Visit 1 consist of the following: screening against inclusion/exclusion; randomization to ECT or standard treatment; and Complete Blood Count (CBC) and coagulation profiles evaluation. An absolute neutrophil count below 1000/mL, a platelet count below 70,000/mL, and/or an international normalized ratio (INR) above 1.5 will be considered exclusion criteria. The patients will be subjected to rectal exploration; rectoscopy; routine hematochemistry and carcinoembryonic antigen (CEA), Magnetic Resonance (MR) with contrast medium (cm) and Computed Tomography (CT) with contrast medium. Medical and Oncology history, including any previous treatments, concomitant treatments, medications, and events will be registered. Pain will be evaluated according to the Visual Analog Scale (VAS) scale and Quality of Life will be monitored according to the EQ5d questionnaire.

All patients will undergo a pre-anesthetic visit and will be excluded from study participation if not eligible for general anesthesia or monitored anesthesia care (conscious sedation).

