#### 2.8.2. Statistical Analysis

The treatment feasibility/safety of surgery following electrochemotherapy will be assessed considering the number of participants with compromised surgery following electrochemotherapy assessed by the R1 resection rate, circumferential resection margin (CRM) involvement, non mesorectal resection plane, and post-operative complications according to the Clavien-Dindo Classification. A surgical complications rate of 30–40% was reported in the literature for conventional neoadjuvant treatment followed by TME [37]. The evaluation of each arm will be performed at Visit 5 (12 weeks from ECT/8 weeks from LE).

Complete response rate (TRG 1 and 2), disease recurrence rates and percentages will be compared among the two groups. A one-sided Fisher exact test will be performed to test the differences between the groups. Differences will be considered significant at *p* < 0.10. A Chi square test will be performed to assess statistically significant differences among the groups for the categorical variable.

The time interval between the recruitment date and local disease progression will be represented using the time of treatment failure and median and minimum–maximum values will be considered.

The scores obtained by the QOL, pain and satisfaction questionnaires will be evaluated. Any serious adverse events and their intensity, according to the NCI-CTCAE classification (version 5.0), will be registered in the first two days post-procedure.

Mean ± standard deviation will be considered for normally distributed continuous variables while the median and interquartile range (IQR) will be presented for non-normally distributed continuous variables.

For continuous variables, the difference between follow-up values and baseline values will be tested by a 2-sided Student t-test or by a Mann–Whitney test while, for the categorical variables, the McNemar test and the marginal homogeneity test will be use [49,50].

Time to event outcomes will be analyzed using the Kaplan–Meier method and survival curves will be compared using the log-rank test.

Mixed effect regression models will be used to analyze longitudinal data by adjusting for proper covariates.

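### The test of follow-up against baseline for continuous variables does not say whether it is within or between arms; naming the baseline-adjusted arm difference for pain and EQ-5D is a free improvement (low priority)

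*Protocol article*

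**What the plan says.** Section 2.1.2 sets the secondary aims: "To evaluate the local recurrence rate, pain control, quality of life and electrochemotherapy toxicity". Allocation is randomised (section 2.2): "Eligible patients will be randomly assigned (1:1) to the treatment group or the control group". Section 2.5 schedules the repeated readings: "Pain will be assessed at Visits 1, 2, 3, 5, 6, 7, 8, 9, 10, 11 and 12". The EQ-5D has the same schedule up to Visit 12 and is optional afterwards. Section 2.5.1 treats Visit 1 as the baseline visit and collects both measures there.

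Section 2.8.2 has three sentences that bear on the analysis:

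- On the scores themselves: "The scores obtained by the QOL, pain and satisfaction questionnaires will be evaluated". No method is attached.
- On continuous variables in general: "For continuous variables, the difference between follow-up values and baseline values will be tested by a 2-sided Student t-test", with Mann–Whitney as the alternative. The same sentence continues, "for the categorical variables, the McNemar test and the marginal homogeneity test will be use".
- At the end of the section: "Mixed effect regression models will be used to analyze longitudinal data by adjusting for proper covariates".

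Elsewhere in 2.8.2, response and recurrence rates are explicitly compared between the two groups, survival curves are compared by log-rank test, and a chi-square test between groups is named for categorical variables. The sentence on continuous variables has no such wording.

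**The concern.** The trial is randomised, so what matters for pain and quality of life is how ECT differs from control. The only test named for continuous variables is described as follow-up against baseline, and its companions for categorical variables, McNemar and marginal homogeneity, are within-patient tests. That points to a before-and-after analysis. Mann–Whitney points the other way, because it is a test for two independent samples and would suit change scores compared between arms. The sentence therefore mixes two designs and does not define the comparison.

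The choice matters because both arms can be expected to change without any ECT effect. All patients have had radiotherapy, all have local excision, and some go on to TME (sections 2.3 and 2.6). A within-arm test responds to that shared change. If a significant change in the ECT arm, or in one arm only, were then taken as evidence about ECT, the inference would not rest on the randomised comparison.

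**Working it through.** **Inputs.** From the document: 70 patients allocated 1:1, so 70/2 = 35 per arm, and a Visit 1 value for pain and EQ-5D. The document gives no SD, correlation, effect size or significance level for these outcomes and no figure for them to reproduce. Assumptions: SD = 1 at each visit; correlation r between baseline and follow-up of 0.3, 0.5 or 0.7; two-sided 0.05 unless stated; one follow-up visit; no dropout.

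**Reading A: tested within each arm.** The SD of the change is √(2(1−r)), which is 1.183, 1.000 or 0.775. For a shift c common to both arms and no ECT effect, the paired t-test has 34 degrees of freedom and noncentrality c√35/√(2(1−r)).

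Chance that the ECT arm is significant although ECT does nothing, with c = 0.5 SD: 68%, 82% or 96% for r = 0.3, 0.5 or 0.7.

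Chance that exactly one arm is significant is 2w(1−w), where w is the single-arm probability. With r = 0.5:

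| Shared shift | w at 0.05 | Exactly one arm | w at 0.10 | Exactly one arm |
|---|---|---|---|---|
| 0.2 SD | 0.210 | 0.33 | 0.316 | 0.43 |
| 0.3 SD | 0.407 | 0.48 | 0.538 | 0.50 |
| 0.4 SD | 0.633 | 0.46 | 0.750 | 0.375 |

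The 0.10 columns are a sensitivity check. Section 2.8.2 states p < 0.10 next to the one-sided Fisher test and attaches no level to the two-sided t-test.

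**Reading B: change scores compared between arms.** A shared shift cancels. In 20,000 simulated trials with a 0.5 SD shift in both arms and no ECT effect, the between-arm test was significant in 4.9% to 5.0%, as it should be. What remains is precision:

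- change-score variance per patient: 2(1−r)
- variance after adjustment for baseline: 1−r²
- ratio: (1−r²)/(2(1−r)) = (1+r)/2

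Power for an assumed arm difference of 0.5 SD uses the noncentral t with 68 degrees of freedom and noncentrality 0.5√(35/2)/s = 2.092/s, where s is the square root of the relevant variance:

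| r | Variance, change | Variance, adjusted | Ratio | Power, change | Power, adjusted |
|---|---|---|---|---|---|
| 0.3 | 1.40 | 0.91 | 0.65 | 41% | 58% |
| 0.5 | 1.00 | 0.75 | 0.75 | 54% | 66% |
| 0.7 | 0.60 | 0.51 | 0.85 | 76% | 82% |

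**The mixed-model sentence.** It could cover either outcome, since both are measured repeatedly. But it names no outcome, arm term, baseline value or visit, and it does not say whether the model or the t-test decides.

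**The case against.** The strongest reply is that the suitable analysis is already there. Section 2.8.2 plans mixed models for longitudinal data, pain and EQ-5D are the obvious candidates, and a full list of model terms is commonly left to a statistical analysis plan that is not shown. Much of this stands, and the absence of model detail is not the point made here. What remains is that the article does state a specific test for continuous variables, leaves its comparison undefined, and does not subordinate it to the model.

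A second reply is that a between-arm comparison of change scores is a legitimate choice for secondary endpoints in a phase II trial. That is right. Under that reading there is no error, only lower precision from a baseline value that is collected anyway.

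A reader might also infer more than the text supports:

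- That the plan has no baseline-adjusted arm comparison at all. The mixed-model sentence may provide one.
- That shared recovery will pass for an ECT effect and power will be lost as well. The first can arise only under the within-arm reading and the second only under the between-arm reading.
- That the plan intends to infer an ECT effect from significance in one arm only. The article nowhere says so.
- That the quoted sentence is explicitly about pain and quality of life. It concerns continuous variables in general. The link is a reasonable inference, since these are the continuous secondary endpoints with a baseline and repeated follow-up.

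**Conclusion.** The point holds as an ambiguity with an easy improvement. The stated test for continuous variables does not say whether it is within or between arms and combines paired and unpaired methods.

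Read within arm, it does not compare the randomised groups. With 35 per arm, an assumed r of 0.5 and no ECT effect, a shared shift of 0.2 to 0.4 SD makes exactly one arm significant in about a third to a half of trials at 0.05. That is harmful only if such a pattern is interpreted as an ECT effect.

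Read between arms, it is valid, and baseline adjustment would cut the variance to 0.65 to 0.85 of the change-score value. For an assumed 0.5 SD difference that is worth 6 to 17 percentage points of power (82−76 to 58−41).

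Every magnitude rests on assumed correlation, shift and effect. Only secondary endpoints are affected; the sample size of 70, the primary endpoint and the interim rule are not. This is a free improvement of low priority.

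**What to change.** In section 2.8.2, name the analysis of pain VAS and EQ-5D as the ECT-minus-control difference from the mixed model already planned. Use arm, visit, arm-by-visit and the Visit 1 value as fixed effects and patient as a random effect. Report the difference with its confidence interval at visits named in advance. State that follow-up-versus-baseline tests within an arm are descriptive and carry no inference about ECT.

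The cost is a change of wording. It needs no new data, visits or patients.

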#### 2.8.3. Interim Analysis

Interim analyses will be fixed after the first step of the study. A conclusive analysis will be performed at the end of the treatment of patients enrolled in the second stage. If a complete response rate to the TRG after local excision is noted in less than 25% of patients in the treatment group, and/or feasibility/safety was not demonstrated, the study will be discontinued. A difference of 20% for both AE rate and surgical complications rate between the two arms will be considered significant enough to discontinue the trial.

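### Within-patient change in continuous outcomes is assigned the Mann–Whitney test for independent samples, and it is left open which of two recurrence analyses decides

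*Protocol article*

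**What the plan says.** All the wording at issue is in section 2.8.2 of the protocol article.

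- **Continuous variables, follow-up against baseline:** "the difference between follow-up values and baseline values will be tested by a 2-sided Student t-test or by a Mann–Whitney test". No arms are named, and the t-test is not called paired or unpaired.
- **Categorical variables, in the same sentence:** "for the categorical variables, the McNemar test and the marginal homogeneity test will be use".
- **Repeated measures:** "Mixed effect regression models will be used to analyze longitudinal data by adjusting for proper covariates".
- **Recurrence as a proportion:** "Complete response rate (TRG 1 and 2), disease recurrence rates and percentages will be compared among the two groups". The next sentence prescribes a one-sided Fisher exact test, with significance at p < 0.10.
- **Time to local progression:** "median and minimum–maximum values will be considered".
- **Time-to-event outcomes:** "Time to event outcomes will be analyzed using the Kaplan–Meier method and survival curves will be compared using the log-rank test".

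Local recurrence, pain control and quality of life are secondary endpoints (section 2.1.2). Pain and EQ-5D are scheduled at eleven visits, 1 to 3 and 5 to 12 (section 2.5).

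**The concern.** A comparison of follow-up with baseline uses two values from each patient. McNemar and marginal homogeneity are tests for such pairs, so the categorical half of the sentence is within-patient and the continuous half reads the same way. Mann–Whitney treats the two sets of values as coming from different people. It ignores the correlation between them and so uses too large a variance for the difference. An unpaired t-test would do the same, and the wording does not exclude one. What is at stake is the p-value and power of the within-patient tests of pain and quality of life.

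The recurrence point is smaller. The section names two analyses for one secondary endpoint: a Fisher test on rates, which takes no account of length of follow-up, and Kaplan–Meier with log-rank, which does. It does not say which counts if they disagree.

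**Working it through.** **Inputs.** The plan gives 70 patients randomised 1:1, so 35 per arm and 35 baseline/follow-up pairs within an arm, and a two-sided test. It states no effect size for pain or quality of life, no baseline-to-follow-up correlation, and no significance level for this two-sided test. Assumed here: normal data with equal SD at both times, a shift of 0.5 SD, 5% two-sided, and correlation r from 0 to 0.7. The plan has no figure of its own on this point to reproduce.

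**Why the size falls.** In SD units, the standard error that an independent-samples test uses for the difference in means is √(2/35) = 0.239. The true standard error for paired data is √(2(1 − r)/35) = 0.239·√(1 − r). Hence, by normal approximation for the t-test:

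- Actual size of the unpaired test = 2[1 − Φ(1.96/√(1 − r))]. This gives 1.9% at r = 0.3, 0.6% at r = 0.5 and 0.03% at r = 0.7.
- Shift over assumed standard error = 0.5/0.239 = 2.092.
- Power of the unpaired test = Φ((2.092 − 1.96)/√(1 − r)): about 56%, 57% and 60%.
- Power of the paired test = Φ(2.092/√(1 − r) − 1.96): about 71%, 84% and 97%.

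**Rank tests by simulation.** 35 pairs per data set; 10,000 data sets per setting for Mann–Whitney and 3,000 for signed-rank.

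| r (assumed) | Power, Mann–Whitney | Power, signed-rank | Size, Mann–Whitney | Size, signed-rank |
|---|---|---|---|---|
| 0 | 51% | 51% | 5.1% | 4.7% |
| 0.3 | 52% | 68% | 1.9% | 4.3% |
| 0.5 | 52% | 79% | 0.8% | 4.8% |
| 0.7 | 54% | 95% | 0.1% | 4.0% |

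A separate run gave 52% v 66%, 54% v 80% and 55% v 95% at r = 0.3, 0.5 and 0.7, with Mann–Whitney sizes of 2.1%, 0.5% and 0.1%. Taken together, power is about 52% v 67%, 53% v 80% and 54% v 95%. The t-tests behave alike: at r = 0.5, 55% unpaired against 81% paired.

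The mean change is the same number whichever test is used. Only its p-value moves.

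**Recurrence.** How far a crude proportion falls short depends on incomplete follow-up. Section 2.4 plans five years for every patient. If all complete it, a crude five-year proportion has no shortfall. With loss, take as an illustration a true five-year rate of 20% and 20% loss over the same period, both at constant hazard. The two hazards are then equal, so recurrence is seen first in half of 1 − 0.8 × 0.8 = 0.36, or 18.0% instead of 20%. With 40% loss the figure is 15.8%. With a true rate of 10% and 20% loss it is 9.0%.

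**The case against.** **Another reading makes Mann–Whitney valid.** If change scores are compared between arms, the two samples are independent. The sentence names no arms, however, and its McNemar half cannot be read that way, so the wording needs correcting even if this was the intention.

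**The plan already holds a sound method.** Mixed models are planned for longitudinal data, and pain and EQ-5D are the repeatedly measured scores. This stands. A reader might infer that real changes in pain or quality of life will be missed, but the documents do not support that, because a method that handles within-patient correlation sits in the same section. The error is also conservative and produces no excess of false positives.

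**Censoring is already handled for recurrence.** Kaplan–Meier and log-rank are stated, and the median and range of failure times do not exclude a Kaplan–Meier median. This largely stands. What it leaves is the missing ranking between the two analyses.

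**Stronger readings of the recurrence text.** Three are tempting, and none is supported.

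- A reader might infer that recurrence will be heavily under-reported because section 2.8.3 says "A conclusive analysis will be performed at the end of the treatment of patients enrolled in the second stage", when the last patients would have little follow-up. That section concerns response, feasibility and safety, and does not say that recurrence is analysed then. Any figure for such a shortfall would rest on an analysis time that the plan does not set for recurrence and on an assumed hazard.
- A reader might infer that the one-sided test would hide an excess of recurrence with ECT. No direction is stated for recurrence, the log-rank test is not called one-sided, and estimates by arm would show an excess whatever the p-value.
- A reader might take the recurrence comparison as a check of local excision against TME. Both arms have local excision (sections 2.3.1 and 2.3.2), so it compares ECT with no ECT.

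**Conclusion.** The point holds in a limited form. Followed as written, section 2.8.2 applies an independent-samples test to within-patient data. At an assumed correlation of 0.5, the nominal 5% test has a true size of 0.5–0.8%, and power is about 53% where the signed-rank test has 80%. The loss is about 15 percentage points of power at r = 0.3 and 41 at r = 0.7, and it vanishes at r = 0. These figures rest on 35 pairs, normal data, a 0.5 SD shift and a correlation that the documents do not give.

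It would go too far to call the secondary results mis-estimated: the estimated change is unbiased and only p-values and power suffer. On recurrence, the finding is confined to two analyses standing side by side with no statement of which decides. The primary TRG comparison is not touched.

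**What to change.** In section 2.8.2:

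1. For within-patient change in continuous variables, replace Mann–Whitney with the Wilcoxon signed-rank test and state that the Student t-test is paired. If a between-arm comparison of change scores was also meant, give it its own sentence that names the arms.
2. State that the between-arm result for pain and quality of life comes from the mixed model already planned, adjusted for baseline.
3. Name Kaplan–Meier with a two-sided log-rank test as the deciding analysis of local recurrence. Remove recurrence from the scope of the one-sided Fisher test, and keep crude percentages as description only.

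This changes wording only. Apart from the signed-rank test, every method is already named in the section. No added patients, visits or data are needed.

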#### 2.8.3. Interim Analysis

Interim analyses will be fixed after the first step of the study. A conclusive analysis will be performed at the end of the treatment of patients enrolled in the second stage. If a complete response rate to the TRG after local excision is noted in less than 25% of patients in the treatment group, and/or feasibility/safety was not demonstrated, the study will be discontinued. A difference of 20% for both AE rate and surgical complications rate between the two arms will be considered significant enough to discontinue the trial.

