### 2.4. Duration of the Study and Follow up

The study will last 36 months with five follow-up years for all patients enrolled. The time for enrolment will be 36 months.

Patients after local excision will be visited every three months in the first two years, and then every six months in the following three years.

This study is subject to stopping rules. Patients can decide to interrupt the treatment. Subjects who discontinue/withdraw from study participation will be evaluated by study personnel.

Starting from the informed consent signature, any event occurring during the treatment phase and/or the follow up phase, will be considered an Adverse Event (AE) and will be recorded. Any clinical or biological abnormalities not present at the trial start will be considered intercurrent events.

The visits scheme is summarized in Table 2.

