**Continuing**										
**Visit #**		10	11	12	13	14	15	16	17	18
**Time**		72 ± 1 week	84 ± 1 week	96 ± 1 week	120 ± 1 week	144 ± 1 week	168 ± 1 week	192 ± 1 week	216± 1 week	240 ± 1 week
	**Visit Description**	Follow up visit	Follow up visit	Follow up visit	Follow up visit	Follow up visit	Follow up visit	Follow up visit	Follow up visit	Follow up visit

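### The only dated final analysis precedes the last patients' Visit 5 and would be premature for recurrence if used for it; the 36 months, five years and week 240 also need reconciling

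*Protocol article*

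**What the plan says.** - **Timing of the final analysis (2.8.3).** "A conclusive analysis will be performed at the end of the treatment of patients enrolled in the second stage". No other final analysis is dated anywhere in the article.
- **Feasibility/safety.** Section 2.1.1 lists it as a primary endpoint. Section 2.8.2 fixes when it is assessed: "The evaluation of each arm will be performed at Visit 5 (12 weeks from ECT/8 weeks from LE").
- **Recurrence.** It is among the secondary endpoints in 2.1.2: "To evaluate the local recurrence rate, pain control, quality of life and electrochemotherapy toxicity". Section 2.8.2 puts it beside response: "Complete response rate (TRG 1 and 2), disease recurrence rates and percentages will be compared among the two groups". A one-sided Fisher exact test at p < 0.10 follows. Later in the same section, Kaplan–Meier curves and the log-rank test are named for time-to-event outcomes. No data cut is given for recurrence.
- **Durations (2.4).** "The study will last 36 months with five follow-up years for all patients enrolled", and then "The time for enrolment will be 36 months".
- **Visits.** Section 2.4: "Patients after local excision will be visited every three months in the first two years, and then every six months in the following three years". The second part of Table 2 schedules Visits 10 to 18 at "72 ± 1 week 84 ± 1 week 96 ± 1 week 120 ± 1 week 144 ± 1 week 168 ± 1 week 192 ± 1 week 216± 1 week 240" weeks, and week 240 is the last visit.

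**The concern.** One date is given for concluding the trial, and three kinds of outcome mature at different times. TRG is read at Visit 4 (Day 37), the surgical feasibility/safety evaluation is made at Visit 5, and local recurrence accrues over years. A cut at the end of stage-2 treatment comes before Visit 5 in the last patients, so a primary endpoint would be incomplete at the analysis meant to conclude on it.

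Recurrence appears in the same sentence as response, so an analyst could reasonably run both comparisons at that cut. Recurrence bears on whether keeping the rectum after ECT and local excision is oncologically safe. A comparison made on a small early share of the events could show no difference for want of data and be read as reassuring. A plain comparison of proportions at that cut would also ignore unequal follow-up.

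The stated durations do not settle when a mature recurrence analysis could be done, because 36 months, five years and week 240 do not fit together as written.

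**Working it through.** **Inputs from the article.** 70 patients (28 + 42); enrolment 36 months; local excision at Day 30; TRG reading at Day 37; Visit 5 at 12 weeks from ECT, 8 weeks from local excision; last visit at week 240; five years of follow-up.

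**Assumptions, not in the article.** Even accrual without a pause; end of treatment taken as local excision; constant recurrence hazard; five-year local recurrence of 5%, 10% or 20%.

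**1. The plan's own follow-up figure.** The text gives 8 visits × 3 months + 6 visits × 6 months = 24 + 36 = 60 months. Table 2 has the same 14 visits (5 to 12 and 13 to 18), but in weeks: 8 × 12 + 6 × 24 = 96 + 144 = 240. The number of visits reproduces; the horizon does not.
- Five years = 5 × 365.25 / 7 = 260.9 weeks.
- From Day 0: 240 × 7 / 365.25 = 4.60 years, short by 260.9 − 240 = 20.9 weeks.
- From local excision: (1680 − 30) / 365.25 = 4.52 years, short by 20.9 + 30/7 = 25.2 weeks.

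**2. Calendar length.** 36 months of enrolment + 60 months of follow-up = 96 months. On the Table 2 schedule it is 36 + 55.2 = about 91 months. Neither is 36.

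**3. Visit 5 at the conclusive cut.** Accrual is 70 / 36 = 1.94 patients a month. Eight weeks is 56 / 30.44 = 1.84 months. 1.94 × 1.84 = 3.6, so about 3 to 4 patients would not have reached Visit 5. Read strictly, the last patient's TRG (Day 37) is also about a week away.

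**4. Follow-up for recurrence at that cut.** Patient i of 70 has 36 − 36i/70 months after local excision.
- Total: 2520 − 1278 = 1242 patient-months; mean 1242 / 70 = 17.7 months.
- Share of the planned 70 × 60 = 4200 patient-months: 29.6%.
- Median 17.7 months overall and 10.5 months in the 42 stage-2 patients.
- 12 of 70 have under 6 months, 23 of 70 have at least 24, and none has 60 (maximum 35.5).

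**5. Events seen at that cut.** Hazard λ = −ln(1 − p)/60 per month; expected events = Σ[1 − exp(−λ × follow-up)].

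| Assumed five-year rate | Events at the cut | Events at five years | Share |
|---|---|---|---|
| 5% | 1.1 | 3.5 | 30% |
| 10% | 2.1 | 7 | 31% |
| 20% | 4.4 | 14 | 32% |

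**6. What the named test could do with so few events.** With 35 per arm and all events in one arm, the one-sided Fisher p-value is:
- 2 v 0: (35/70)(34/69) = 0.246
- 3 v 0: 0.246 × 33/68 = 0.120
- 4 v 0: 0.120 × 32/67 = 0.057

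At least four events, all in one arm, are needed for p < 0.10. At assumed rates of 5% or 10%, fewer than that are expected in both arms together.

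**The case against.** The conclusive-analysis sentence stands in the interim-analysis section, between rules on TRG response and safety. The group-sequential design in 2.8.1 is built on TRG. Read there, the sentence is the counterpart of the interim look and was probably written with TRG in mind.

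A reader might infer more than the article supports on four points:

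- **That recurrence is concluded at this cut and later data go unanalysed.** No section says so. Section 2.8.2 plans Kaplan–Meier, log-rank and longitudinal models without a date, and a full protocol or SAP could set one. The absence of a recurrence date is not itself the finding.
- **That 36 months truncates follow-up.** The same sentence grants five years to every patient. Enrolment for 36 months followed by five years is a coherent reading, and what remains is loose wording.
- **That the missing visit defeats a five-year estimate.** No five-year landmark is named as an endpoint. The gap comes from writing 3 and 6 months as 12 and 24 weeks and counting from ECT. It is minor.
- **That timing alone makes the recurrence comparison weak.** Even complete follow-up gives only 3.5, 7 or 14 events under the assumed rates, so it would be imprecise at any cut in a trial of 70. Log-rank handles unequal follow-up, though it cannot supply events not yet observed.

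The end of treatment is also undefined. If it included a TME planned after histology, the cut would be later for patients who have one.

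What the objection leaves standing is that 2.8.3 does state a date, that this date conflicts with Visit 5 for a primary endpoint, and that the stated durations disagree.

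**Conclusion.** The point holds in limited form. As written, 2.8.3 places the only dated final analysis about 8 weeks before the last patients reach the visit at which 2.8.2 evaluates a primary endpoint. That affects about 3 to 4 of 70 patients under even accrual, with local excision as the end of treatment.

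The recurrence consequence is conditional. If recurrence is tested at the same cut, follow-up ranges from about 0 to 3 years (mean about 18 months) and about 30% of five-year events are seen. That share changes little across assumed five-year rates of 5% to 20%, but it rests on even accrual and a constant hazard. The article does not commit to that use of the cut, and it does not rule it out.

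The 36-month figure used for both study and enrolment, and a last visit 21 weeks short of five years from Day 0 (25 from local excision), are inconsistencies of wording and labelling. The TRG comparison itself is affected only through the last patient's reading, about a week after excision.

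**What to change.** - **2.8.3:** time the primary analysis of TRG and feasibility/safety at the point when the last randomised patient has completed Visit 5.
- **2.8.3:** set a separate final analysis of local recurrence and the other time-to-event outcomes after the last patient's final follow-up visit. Label any recurrence figure reported earlier as immature and descriptive.
- **2.4:** state the duration as 36 months of enrolment plus follow-up, about 96 months if five years is meant or about 91 on the Table 2 schedule.
- **2.4 and Table 2:** reconcile the week-240 last visit with the five follow-up years, and state whether the horizon counts from Day 0 or from local excision.

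**Cost.** The primary analysis moves about 8 weeks later, the stated study duration becomes longer, and one later analysis is run on data the trial already collects. No patients are added.
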